| Rapid test for malaria parasites (for ACD)       |                |                |                |                |                |                |                | ● H | ● H | ● H | ● H | ● H | ● H | ● S | ● H | ● R |
| Parasite Genotyping (for ACD)                    |                |                |                |                |                |                |                | ● H | ● H | ● H | ●              | ● H | ●              | ● S | ● H | ● R |
| Passive Case Detection J              |                | ●              | ●              | ●              | ●              | ●              | ●              | ●              | ●              | ●              | ●              | ●              | ●              | ●              | ●              | ●              |
| SAFETY LABS                               |                |                |                |                |                |                |                |                |                |                |                |                |                |                |                |                |
| Complete blood count K                | ●              |                |                |                |                |                |                |                | ●              |                | ●              |                | ●              |                |                |                |
| Creatinine, ALT                                  | ●              |                |                |                |                |                |                |                | ●              |                | ●              |                | ●              |                |                |                |
| Hemoglobin                                |                |                |                |                |                |                |                |                |                |                |                |                |                |                |                | ● R |

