**Amended 17 April 2008**

**CONFIDENTIAL**

106464 (Malaria-049)  
Amendment 4 Final, 17 April 2008

ACD: Active Case Detection PCD: Passive Case Detection ICS: Intracellular Cytokine Staining FW: Field Worker

A The survey will be postponed in the event of low case rates occurring during the first four months of surveillance

B These visits will occur in the double blind phase in the event that the survey at Clinic Visit 6 is postponed

C all antimalarial, systemic antibiotic and antipyretic medication to be recorded

D record administration of immunosuppressants or other immune-modifying drugs during this period (for corticosteroids this means prednisone or equivalent,  $\geq 0.5$  mg/kg/day. Inhaled or topical steroids are allowed and should not be recorded. ALSO all immunoglobulins and blood products should be recorded during this period. ALSO any antimalarials.

E SAEs related to study procedures will be collected

F Procedure for PCD will be followed

Amended 20 November 2006

H If documented fever

J Where the subject is febrile, blood test, rapid test, and parasite genotyping will be performed

K Includes analysis of hemoglobin, total white cell count and platelets.

L Done only in study participants enrolled by KEMRI, Kenya

M Final analysis will be delayed in the event of low case rates occurring during the first four months of surveillance

N Visit 39 to occur between 14 days post Dose 3 of vaccine and 20 days post Dose 3 of vaccine

O Carried out on Field Worker Visit Code # 55 ONLY

P Carried out on Field Worker Visit Code # 86 ONLY

Amended 23 October 2006

Q Samples from Tanzania will be analyzed at LSHTM and/or their collaborating laboratory, at GSK Biologicals and/or their collaborating laboratory, and in Tanzania. Samples from Kenya will be analyzed at LSHTM and/or collaborating laboratory, at GSK Biologicals and/or collaborating laboratory, and in Kenya

Amended 20 November 2006

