**Clinic Visit 5: Cross-sectional visit for ACD**  
Day 90

---

- Check study identification card of vaccinee.
- Carry out physical examination.
- Record SAEs experienced by the vaccinee since the last visit.
- Record unsolicited adverse events experienced by the vaccinee since the last visit.
- Check elimination criteria.
- Record concomitant medication.
- Record axillary temperature of subject.
- Blood sample to collect 5 mL blood for analysis of:
  - hematology (complete blood count).
  - biochemistry (creatinine and ALT).
  - serology (antibodies to CS, HBs, anti-blood-stage humoral immunity).

- CMI:  
CS-specific T-cells (ICS);  
*At KEMRI, Kenya only: CS-specific T-cells (ELISPOT).*
- *In addition, blood will be drawn from all subjects for:*
  - Rapid test for malaria parasites (only if subject is febrile).
  - Blood slide for malaria parasites.
  - Blood test for malaria parasite genotyping.
  - Complete Blood Count.

Amended 20 November 2006

---

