**Safety**

- Occurrence of solicited symptoms and local reactions over a 7-day follow-up

period (day of vaccination and 6 subsequent days) after each vaccination.

- Occurrence of unsolicited symptoms over a 30-day follow-up period (day of vaccination and 29 subsequent days) after each vaccination.
- Occurrence of serious adverse events from the time of first vaccination (Month 0) until 4½ months post Dose 3 (Month 6½).
- Occurrence of parameters of hematological monitoring outside acceptable ranges.

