#### **10.10.4. Analysis of safety**

##### **10.10.4.1. Secondary safety endpoints**

Safety will be analyzed on the Total Vaccinated Cohort. If the percent of enrolled subjects excluded from the ATP cohort for analysis of safety is more than 5%, a second analysis based on this ATP cohort will be performed to complement the Total Vaccinated Cohort analysis.

Analysis of the occurrence of SAEs will be performed on the Total Vaccinated Cohort. The proportion of subjects with an SAE, classified by the MedDRA preferred term level, reported from study start until Clinic Visit 6 (end of the double-blind phase) will be tabulated with exact 95% CI.

The proportion of subjects reporting an AE (unsolicited) 30 days post each vaccination, classified by the MedDRA preferred term level, reported from study start until the end of the double-blind phase will be tabulated with exact 95% CI.

The percentage of subjects with at least one local adverse event (solicited and unsolicited), with at least one general adverse event (solicited and unsolicited) and with any adverse event during the solicited follow-up period will be tabulated with exact 95% CI after each vaccine dose and overall. The percentage of doses followed by at least one local adverse event (solicited and unsolicited), by at least one general adverse event (solicited and unsolicited) and by any adverse event will be tabulated, overall vaccination course, with exact 95% CI. Similar tables will be generated for Grade 3 events, the relationship of the event to vaccination.

The percentage of subjects reporting each individual solicited local and general adverse event during the solicited follow-up period will be tabulated with exact 95% CI. The percentage of doses followed by each individual solicited local and general adverse event will be tabulated, overall vaccination course, with exact 95% CI. Similar tables will be generated for Grade 3 events, the relationship of the event to vaccination and for fever and temperature in 0.5°C increments.

Biochemistry (ALT and creatinine) and hematology (hemoglobin, WBC, platelets) values that are outside of the reference ranges will be described for Clinic Visit 6 (end of double-blind phase). Frequency distribution of results by toxicity grades will be tabulated by group.

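### The planned laboratory safety tables name only Clinic Visit 6; no group summary is planned for the same tests at Clinic Visit 5, 21 to 42 days after Dose 3

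*Protocol*

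**What the plan says.** Section 10.10.4.1 covers five laboratory parameters: ALT, creatinine, hemoglobin, white cells and platelets. It says that "values that are outside of the reference ranges will be described for Clinic Visit 6 (end of double-blind phase"). The next sentence reads "Frequency distribution of results by toxicity grades will be tabulated by group" and names no visit. The presentation is descriptive, and no test is planned.

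The laboratory endpoint in section 10.2 is "Occurrence of parameters of hematological monitoring outside acceptable ranges". It has no visit limit and names hematology only. The secondary safety objective in section 2.2 runs to 4½ months after Dose 3, and the SAE endpoint in 10.2 places that time at "until 4½ months post Dose 3 (Month 6½").

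The visit description for Clinic Visit 5 (section 5.14) includes "hematology (complete blood count") and "biochemistry (creatinine and ALT"). In Table 3 the row "Creatinine, ALT" is marked at Clinic Visits 1, 5, 6 and 7, and the complete blood count row carries the same marks. A note to Table 3 says of the Clinic Visit 6 survey: "The survey will be postponed in the event of low case rates occurring during the first four months of surveillance".

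The safety part of the annex analysis (10.11.2) covers SAEs only. Section 10.9.3, applied again through 10.11.1, compares hemoglobin between groups at Clinic Visit 6, Month 14 and Clinic Visit 9 as an efficacy endpoint.

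**The concern.** The full panel is drawn three times after vaccination, and the laboratory safety analysis names the middle draw. That draw is months after the last dose, and its date can move later with malaria incidence. The draw nearest to dosing is taken, and it falls within both the safety objective and the hematology endpoint, but no group table is planned for it.

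At stake is whether the final report can show a transient laboratory difference between the vaccine and control groups. If ALT, creatinine or a blood count differs a month after Dose 3 and then recovers, the planned laboratory tables would not show it. Section 4.4 excludes children whose screening values lie outside the Table 9 limits, so out-of-range values at Visit 5 would be largely new since screening. That makes the visit informative.

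**Working it through.** The plan states no statistical figure on this point, so the check is of visit timing and of which draws each analysis section covers.

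**Timing.** Dose 3 is at Clinic Visit 4 (Day 60, Month 2).

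- Clinic Visit 5: Day 90 − Day 60 = 30 days. Table 4 allows 21 to 42 days.
- Clinic Visit 6: Month 6½ − Month 2 = 4½ months, and 4.5 × 30.4375 ≈ 137 days. This is a minimum, because the survey may be postponed.
- Clinic Visit 7: Month 14 − Month 2 = 12 months.
- Gap from Visit 5 to Visit 6: nominally 6½ − 3 = 3½ months. Over the Visit 5 window it is 137 − 42 = 95 days to 137 − 21 = 116 days, and longer if Visit 6 is postponed.

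**Planned group summaries after vaccination.**

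| Parameter | Visit 5 | Visit 6 | Visit 7 |
|---|---|---|---|
| ALT | none | 10.10.4.1 | none |
| Creatinine | none | 10.10.4.1 | none |
| White cells | none | 10.10.4.1 | none |
| Platelets | none | 10.10.4.1 | none |
| Hemoglobin | none | 10.10.4.1 and 10.9.3 | 10.9.3 and 10.11.1 (efficacy) |

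Five parameters at three draws make 5 × 3 = 15 combinations. Covered: 0 at Visit 5, 5 at Visit 6 and 1 at Visit 7, so 6. Not covered: 15 − 6 = 9, of which 5 are at Visit 5 and 4 at Visit 7.

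**Sensitivity to the reading of the toxicity-grade sentence.** The table above takes that sentence to continue the Visit 6 sentence before it. If it is read instead as covering every laboratory draw up to Visit 6, the five Visit 5 combinations gain a grade table. Coverage becomes 6 + 5 = 11 of 15. The out-of-range description at Visit 5 and the four Visit 7 combinations still have nothing planned.

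**Do adverse event tables fill the gap?** Section 8.3 requires abnormal results that the investigator judges clinically significant to be recorded as AEs or SAEs if they meet the definition. Unsolicited AEs in section 10.2 cover the day of vaccination and the next 29 days, so after Dose 3 to Day 60 + 29 = Day 89. The nominal Visit 5 draw is on Day 90, and the window runs to 42 days after Dose 3. A non-serious abnormality first found at Visit 5 can therefore fall at or beyond the edge of AE capture. SAEs are captured throughout. AE recording depends on clinical judgment, which a table of grades does not.

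**The case against.** Five points can be made for the plan.

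- **Nothing excludes Visit 5.** The toxicity-grade sentence names no visit, the endpoint has no visit limit, and section 10.10 bases the final analysis on data collected up to Clinic Visit 6, which includes Visit 5. The wider reading is possible. It stands as an ambiguity, but the grade sentence directly follows one that fixes the visit, and nothing extends it.
- **This is detail for the analysis plan.** Section 6.5 promises a reporting and analysis plan, which is not at hand and could add visits. That would answer a protocol that was silent on visits. This one names a single late visit, so an analysis that follows it omits Visit 5.
- **Other safeguards exist.** Results are reviewed child by child as generated (5.5), and clinically significant abnormalities can be reported as AEs or SAEs and tabulated. This stands, and it narrows the gap mainly to changes not judged clinically significant and to non-serious findings outside AE capture. It does not replace a group table.
- **Visit 7 is of less interest.** It is 12 months after Dose 3, and hemoglobin there is compared between groups. This stands, and it is why Visit 7 is only an optional part of the fix.
- **Prior safety review.** Section 1.6 says the vaccine is first tested in children aged 5 to 17 months in Ghana, with unblinded safety data reviewed by the DSMB before this trial proceeds. This reduces the concern but does not bear on how this trial's own data are reported.

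A reader might infer that laboratory values at Visits 5 and 7 are never compared by group, or that any early abnormality is invisible. The documents support neither: hemoglobin is compared at Month 14, and clinically significant abnormalities can surface as AEs or SAEs.

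**Conclusion.** The gap is real and modest. As written, section 10.10.4.1 describes out-of-range laboratory values only at Clinic Visit 6, at least 4½ months after Dose 3. No section plans a group summary of any laboratory value at Clinic Visit 5, or of ALT, creatinine, white cells or platelets at Clinic Visit 7. That is 9 of 15 post-vaccination combinations, with the five at Visit 5 mattering most. An abnormality seen at Visit 5 that resolves over the following 3½ months or so would be in no planned group laboratory table.

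This rests on reading the toxicity-grade sentence with the Visit 6 sentence before it. It does not assume that a vaccine effect exists. That such an effect would more likely show soon after dosing is an assumption the documents do not state. The case for the change needs only that Visit 5 lies within the safety objective and is drawn for safety. The shortfall is in descriptive reporting; no planned test is lost, because none is planned at Visit 6 either.

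**What to change.** In section 10.10.4.1, state that out-of-range biochemistry and hematology values are described, and toxicity grades tabulated by group, at Clinic Visit 5 as well as Clinic Visit 6. Naming both visits in the toxicity-grade sentence also removes the ambiguity. Optionally, add the Clinic Visit 7 safety laboratory values to section 10.11.2.

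The cost is a few extra descriptive tables. The blood draws are already scheduled and section 5.5 already requires the results on the CRF, so no procedure, sample or visit changes.

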## **10.11. Annex analysis at study conclusion**

### **10.11.1. Analysis of efficacy**

Analysis of efficacy will be performed on the ATP Cohort for Efficacy and Total Cohort. Vaccine efficacy endpoints:

- time to first/only case of malaria.
- multiple events of malaria.
- parasite prevalence and density.
- hemoglobin values.

will be analyzed according to methods described in Section 10.9.

### **10.11.2. Analysis of safety**

Analysis of the occurrence of SAEs will be performed on the Total Vaccinated Cohort. The proportion of subjects with an SAE, classified by the MedDRA preferred term level, reported from study start until Clinic Visit 7 *and from study start until Clinic Visit 9* will be tabulated with exact 95% CI.

*Amended 17 April 2008*

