Subsequently, a large safety, immunogenicity and efficacy trial in children aged 1 to 4 years from an area of high transmission was conducted in Mozambique, enrolling a total of 2022 subjects (Malaria-026 [Report, GSK data on file]; [Alonso 2004]; [Alonso 2005]). In this study, 3 doses of RTS,S/AS02A (0.25 mL dose) were administered according to a 0, 1, 2-month schedule to approximately 1000 children. The primary endpoint of this trial investigated vaccine efficacy against the onset of clinical malaria disease. Up to six months post Dose 3, the VE determined as the time to the first clinical episode (after adjustment for covariates) was 29.9% (95% CI: 11.0 to 44.8;  $p = 0.004$ ). For the entire study period, up to 18 months post Dose 3, VE for the same endpoint was 32.8% (95% CI: 20.1 to 43.4;  $p = 0.0001$ ).

The trial also offered the opportunity to investigate VE against multiple attacks of malaria and severe malaria. Against multiple attacks, VE was 27.4% (95% CI: 6.2 to 43.8;  $p = 0.014$ ) up to six months post Dose 3. For the entire study period, VE was 32.4% (95% CI: 17.6 to 44.5;  $p = 0.0001$ ). Against severe malaria, VE was 57.7% (95% CI: 16.2 to 80.6;  $p = 0.019$ ) over six months post Dose 3: for the entire study period VE was 48.6% (95% CI 12.3 to 71.0;  $p = 0.02$ ).

During the single-blind phase (Months 8½ to 21) in both Cohort 1 and 2, the proportion of children experiencing a SAE was similar in the RTS,S/AS02A and control groups

(5.1% vs. 6.8%, respectively). However, in the overall surveillance period (Months 0 to 21), there was a tendency for the proportion of children experiencing a SAE to be lower in the RTS,S/AS02A group compared to the control groups in both Cohorts 1 and 2 (20.9% vs. 28.6%, respectively). The pattern of morbidity was similar to that previously observed at the study site and described in the region. At least 97% of recipients of RTS,S/AS02A were seropositive for anti-CS antibodies and at least 97% of recipients of RTS,S/AS02A were seroprotected for anti-HBs antibodies 18 months post Dose 3 [Alonso, 2005].

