### 2.3. Tertiary objectives

- For RTS,S/AS01E when administered as three doses intramuscularly on a 0, 1, 2-month schedule to children aged 5 to 17 months living in malaria-endemic areas:
  - to assess efficacy against clinical malaria disease (detected on active and passive case detection) with *P. falciparum* over a period of 12 months post

Dose 3.

- to assess safety between 4½ months post Dose 3 and 12 months post Dose 3.
- *To assess safety until October 2008 in Kilifi and September 2008 in Korogwe.*

*Amended 17 April 2008*

- *To assess efficacy against clinical malaria (detected on active and passive case detection) with P. falciparum from Dose 3 until October 2008 in Kilifi and September 2008 in Korogwe.*

*Amended 17 April 2008*

- to assess antibody responses to the circumsporozoite (CS) antigen at 12 months post Dose 3.
- to assess antibody responses to the hepatitis B surface (HBs) antigen at 12 months post Dose 3.
- *to assess antibody responses to the circumsporozoite (CS) antigen at a cross-sectional survey occurring in October 2008 in Kilifi and September 2008 in Korogwe.*

*Amended 17 April 2008*

- to assess the T-cell immune response to CS antigen up to 12 months post Dose 3 in an Intracellular Cytokine Assay.

Refer to Section 10.3 for definitions of tertiary endpoints.

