#### **Safety**

- Occurrence of SAEs throughout the entire study period.

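### The objective is safety between 4½ and 12 months after Dose 3, but every planned SAE table runs from study start, so none estimates SAE occurrence in that interval

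*Protocol*

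**What the plan says.** - **Objective.** Protocol Section 2.3, like the Synopsis, lists as a tertiary objective "to assess safety between 4½ months post Dose 3 and 12 months post Dose 3". This is a bounded interval. Amendment 4 added a second safety objective running to the end of the extension in September or October 2008.
- **Endpoint.** Section 2.3 points to Section 10.3, where the only tertiary safety endpoint is "Occurrence of SAEs throughout the entire study period".
- **Double-blind SAE table.** Section 10.10.4.1 plans the proportion of children with an SAE, by preferred term, "reported from study start until Clinic Visit 6 (end of the double-blind phase) will be tabulated with exact 95% CI".
- **Annex SAE tables.** Section 10.11.2 plans "The proportion of subjects with an SAE, classified by the MedDRA preferred term level, reported from study start until Clinic Visit 7". Amendment 4 then put in a second window, equally cumulative: "and from study start until Clinic Visit 9". Both tables use the Total Vaccinated Cohort and carry exact 95% CI.
- **Timing of Visit 6.** A note to Table 3 lets the Clinic Visit 6 survey be postponed if case rates are low in the first four months of surveillance.
- **Earlier trial.** Section 1.4 reports SAEs in the Mozambican children's trial in two windows. For the later one ("During the single-blind phase (Months 8½ to 21) in both Cohort 1 and 2") the proportions were "5.1% vs. 6.8%, respectively", vaccine then control. For the whole period they were 20.9% vs 28.6%, described thus: "in the overall surveillance period (Months 0 to 21), there was a tendency for the proportion of children experiencing a SAE to be lower".

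**The concern.** The objective asks about one period after vaccination, and every SAE window that the protocol fixes starts at study start. A cumulative proportion of children ever affected cannot answer an interval question, for three reasons:

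- A child with an early SAE is already counted. A later SAE in that child adds nothing to the any-SAE proportion, and nothing to the row for the same preferred term.
- The early phase is part of both arms' figures. If the vaccine reduces early SAEs, that reduction dilutes or offsets a late excess in the overall proportion and in malaria-related terms.
- No interval estimate, and so no confidence interval for it, is produced.

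Section 1.6.4 treats duration of protection as an open matter, so the later interval needs a safety result of its own. As planned, the annex report could not give one directly.

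**Working it through.** **Windows side by side**

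| Item | Start | End |
|---|---|---|
| Objective, 2.3 | 4½ months post Dose 3 | 12 months post Dose 3 |
| Endpoint, 10.3 | study start | study end |
| Table, 10.10.4.1 | study start | Clinic Visit 6 |
| Table 1, 10.11.2 | study start | Clinic Visit 7 |
| Table 2, 10.11.2 | study start | Clinic Visit 9 |

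No endpoint or table begins where the objective begins.

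**How far a cumulative table can differ from an interval table.** The protocol gives no expected SAE rate or power for SAEs, so there is no figure of its own to reproduce on this point. As a check on the method, exact enumeration of the two-sided Fisher test reproduces the stated 90% power for the primary comparison: 0.902 at 400 per group, 36% vs 25.2%.

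Inputs, all from Section 1.4, vaccine vs control: late 5.1% vs 6.8%; whole period 20.9% vs 28.6%. Group size is 445 (Synopsis). Assumption: within each arm, early and late SAE risks are independent.

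1. Early risk = 1 − (1 − total)/(1 − late).
   - Vaccine: 1 − 0.791/0.949 = 16.6%.
   - Control: 1 − 0.714/0.932 = 23.4%.
2. Suppose the late vaccine-arm risk were twice control: 2 × 6.8% = 13.6%.
   - Cumulative, vaccine: 1 − (0.791/0.949) × (1 − 0.136) = 28.0%.
   - Cumulative, control: 28.6%.
   - An interval table at 445 per group would show about 61 vs 30 children, 13.6% (95% CI 10.7 to 17.3) vs 6.8% (4.6 to 9.5).
3. Suppose it were 1.5 times control: 10.2%.
   - Cumulative: 25.2% vs 28.6%, which leans towards the vaccine.
   - Interval: 10.2% vs 6.8%, about 45 vs 30 children, Fisher p = 0.09. The interval table would show this excess but would not be conclusive.
4. The cumulative proportions are equal at a late risk of 1 − 0.714/(0.791/0.949) = 14.3%, a ratio of 14.3/6.8 = 2.1.

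**Sensitivity of the doubling scenario**

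- *Early and late SAEs in different children.* Early risk is 20.9 − 5.1 = 15.8% vs 28.6 − 6.8 = 21.8%. Cumulative: 15.8 + 13.6 = 29.4% vs 28.6%.
- *Scaled to this trial's windows.* The scaled risk is 1 − (1 − p)^f, with f = 6.5/8.5 early and 7.5/12.5 late, assuming constant hazard. Interval: 8.3% vs 4.1%. Cumulative: 20.2% vs 21.8%.
- *No early benefit.* Cumulative: 33.8% vs 28.6%, a ratio of 1.18 against 2.0 in the interval. The excess is diluted but not cancelled.

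Power of a two-sided Fisher test on the interval figures under doubling is 0.91 at 445 per group, 0.87 at 400, and about 0.69 at 445 after scaling. No test is planned for SAEs, so power here only gauges how visible a doubling would be.

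**What the planned tables recover together.** Under doubling with independence, subtracting the Visit 6 proportions from the Visit 7 proportions gives about 11.3% vs 5.2% newly affected. This leaves out late SAEs in children with an earlier one and has no confidence interval.

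**The case against.** The strongest case is that this is a wording mismatch. Section 2.3 refers to 10.3, and 10.11.2 analyses the endpoint given there. A separate analysis plan may add table cuts, and the DSMB is informed of all SAEs in any case.

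A reader might infer that late safety goes unanalysed and that a doubling of late SAEs would be hidden. The documents do not support that:

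- The Visit 6 and Visit 7 tables together show newly affected children, and in the doubling scenario their proportion is more than twofold higher in the vaccine arm.
- SAEs are classified by preferred term. A late excess in a non-malaria term could appear in its own row, because no prevented malaria offsets it there.
- Malaria after the early period is also followed through the 12-month efficacy endpoints (10.3) and the checks for time-varying efficacy (10.9.1), although these are not specific to SAEs.

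Nor does the earlier trial demonstrate masking. Its late ratio is 5.1/6.8 = 0.75 and its overall ratio 20.9/28.6 = 0.73, which are nearly the same. It used another adjuvant, in children aged 1 to 4 years, over a late window of 12.5 months against about 7.5 here. The doubling lies close to the break-even ratio of 2.1, so near-cancellation follows partly from that choice. The power of 0.91 rests on unscaled rates and full follow-up.

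All of this limits the size of the point. The mismatch itself stands: the protocol names its SAE windows, and none is the interval in the objective. An unseen analysis plan could add a table, but the windows fixed here would still not match the objective.

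**Conclusion.** The point holds as a mismatch between a stated objective and the analyses fixed for it. No planned table estimates SAE occurrence between 4½ and 12 months after Dose 3. What the planned tables lose is late SAEs in children already affected, a confidence interval for the interval, and a clean reading where an early reduction and a late excess fall in the same row, above all in malaria-related terms.

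The size is illustrative only. It rests on borrowed rates, on independence of early and late risk, and on a hypothetical doubling. Under those assumptions a cumulative 28.0% vs 28.6% stands against an interval 13.6% vs 6.8%. Nothing in the documents suggests that a late excess exists. The objective is tertiary and the data remain recoverable, so this should be corrected but does not threaten the trial's main conclusions.

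**What to change.** In Section 10.11.2 keep the cumulative tables and add, by group with exact 95% CI, the proportion of children with an SAE with onset:

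1. from 4½ to 12 months after Dose 3; and
2. from 12 months after Dose 3 to Clinic Visit 9, for children in the extension.

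Date both windows from Dose 3, not from Clinic Visit 6, so that postponing that visit does not move the interval. The denominator is children under follow-up at the start of each interval. A child with an earlier SAE is counted again if a new one starts in the interval. Because the cohort is the Total Vaccinated Cohort, state a substitute reference date for children who did not receive Dose 3, as Section 10.9.4 does for time at risk.

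Separately, the Synopsis and Section 3 end SAE capture 12 months after Dose 3, while Section 10.11.2 tabulates SAEs to Clinic Visit 9 and Section 5.14 records them at Visits 8 and 9. These passages must be reconciled.

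The cost is one or two descriptive tables built from onset dates already recorded under Section 8.4. No new data or visits are needed.
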